### Data acquisition, data management and data archiving

Participant data will be collected using a Primary Data Collection Tool based on MEDITyme^®^ platform technology as a web-based application, supplied by XPERTyme GmbH (Wessling, Germany). The platform has been developed to incorporate all the necessary features to enable secure video communications and to support the compliant collection, transmission, and storage of study data. It is designed to ensure compliance with Good Clinical Practice (GCP) and General Data Protection Regulation (GDPR) requirements. All source data and informed consent forms will be directly documented and stored on the platform, following predefined standardised processes. Since no additional source data are generated at the study sites, on-site monitoring is not required. In order to minimise errors in data entry and ensure data quality, the system incorporates predefined data entry rules and validation checks. Access to the platform is restricted to authorised study personnel and participants according to predefined roles and responsibilities and blinding specifications. For example, group therapists and group facilitators are only permitted to see the data of their own group participants. Any subsequent corrections are digitally documented and fully traceable through an audit trail. The group sessions and qualitative interviews will be recorded and subsequently stored in order to facilitate the supervision and qualitative analysis of the data.

The process evaluation will be conducted through continuous monitoring of data integrity, adherence to the informed consent procedure, and verification of protocol compliance by the Principal Investigator (PI), who has full access to all study data of all participants. Protocol deviations identified during monitoring will be documented and addressed according to CAPA (Corrective and Preventive Action) procedures.

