### Safety considerations

As part of the contact email sent to interested participants, a link is provided to a PDF containing information on always-available support services for crisis situations. In case of concerns or questions, participants may contact the research team at any time via email or by phone during designated office hours, or reach out to their group therapist or group facilitator during group or individual sessions, or through the messaging function within the Primary Data Collection Tool. Within the group sessions in both programmes, concepts for following supportive treatments are discussed, but such services are not directly provided or arranged for the participants.

The Primary Data Collection Tool facilitates the documentation of safety-relevant data that could potentially lead to an early termination of the study (see the section below for more information). An adverse event (AE) is defined as any undesirable experience that occurs to a participant during the trial and that may affect the intervention itself, the exclusion criteria or the participant’s ability to continue participating in the study. These events can be reported by participants or group therapists, group facilitators, or research team members at any time point during the study in the Data Collection Tool. Participants are regularly reminded of this option in the group sessions. Serious adverse events (SAEs), i.e. breach of trust in the study members, acute worsening of depressive symptoms, hospitalisation, self-harm, suicide attempts or suicide, will be documented in the case report form and reported to the main study site (MSB).

The study will also be monitored by an Independent Data and Safety Monitoring Board (IDSMB) specifically chosen to include a geriatrician, a geropsychiatric, a statistician and a clinical psychologist, ensuring the utmost competence and vigilance. The IDSMB will meet via videoconference before, during and after the trial to review its progress and provide an independent evaluation of the safety of the participating patients (especially in the event of SAEs) and adherence to the protocol (data integrity and the validity of the clinical trial). If necessary, the frequency of the web conferences can be increased. The study will only continue if it is deemed safe by the IDSMB, which can also provide the sponsor with information and make recommendations.

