### Termination criterion

If a participant withdraws their informed consent during the study, as termination criteria, all data collected up to that point will be removed from the analysis dataset, with the deletion duly documented.In addition, participation in the study may be terminated early under the following circumstances:If a participant does not wish to continue participating or cannot be reached, or fails to attend required study visits (drop-out);If a participant starts an ambulant psychotherapy between the assessment points T0 and T7;If a participant changes their psychoactive medication, continued study participation will be reviewed on a case-by-case basis in consultation with the participant and PI;If health problems arise that are not related to the study content, but may hinder focus-targeted or regular study participation, continued study participation will be reviewed on a case-by-case basis in consultation with the participant and PI. This includes new or worsening physical complaints (e.g. a fall followed by hospitalization), serious events (e.g. the unexpected death of a family member) or psychological complaints (e.g. acute grief – except for depression and anxiety, which are dealt with under point [f]);If any SAE occur, decisions regarding continued participation will always be made by the PI in consultation with the IDSMB, to ensure the participant’s well-being and the appropriateness of their involvement. The jointly made decision will be transparently communicated to the participant;If a participant passes away during the study period;If the PI or study sponsor decides to discontinue participation for specific reasons.

In the event of early termination, the termination criteria are recorded on an individual basis, specifying the corresponding time point and category.

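### The closed list of serious adverse events contains no death other than suicide, so a death from another cause without hospital admission has no mandatory SAE report

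*Protocol article*

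**What the plan says.** Four parts of the protocol article bear on this.

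- **SAE definition and handling (Safety considerations).** SAEs are defined as "i.e. breach of trust in the study members, acute worsening of depressive symptoms, hospitalisation, self-harm, suicide attempts or suicide". Events on this list "will be documented in the case report form and reported to the main study site (MSB").
- **Ordinary adverse events (same section).** The AE definition is broad enough to cover a death. The reporting sentence is permissive: "These events can be reported by participants or group therapists, group facilitators, or research team members at any time point during the study".
- **Monitoring board (same section).** The IDSMB is to give an "independent evaluation of the safety of the participating patients (especially in the event of SAEs") and to look at adherence to the protocol. The study continues only if the board considers it safe.
- **Termination criterion.** Death has its own entry, "If a participant passes away during the study period", separate from the entry for SAEs. Only the SAE entry requires the investigator to decide together with the IDSMB. For every early termination, "the termination criteria are recorded on an individual basis, specifying the corresponding time point and category". Another entry covers health problems unrelated to the study content. Its example is "new or worsening physical complaints (e.g. a fall followed by hospitalization"), and its stated route is a case-by-case review by participant and investigator.

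The section on data acquisition adds that the principal investigator is the person "who has full access to all study data of all participants".

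**The concern.** The list is introduced as a restatement of what an SAE is, not as a set of examples, so an event outside it is not an SAE. A breach of trust is then serious, while a sudden cardiac death at home is not.

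The trial enrols people aged 68 and over with no upper age limit, so deaths from natural causes are foreseeable. The board's judgement on whether the study is safe to continue should rest on every death by arm. Under the text as written, some deaths could be missing from the SAE count and from the review that SAEs trigger.

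A rule that depends on cause is also awkward in a depressed population. When someone is found dead at home, the cause may be unclear at first, yet the list makes reporting mandatory only once the death is taken to be suicide. Reporting every death removes that judgement and so also protects the capture of suicides.

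The hospitalised fall raises a lesser question. It is an SAE by the list, but the termination section uses it to illustrate a route that does not mention the IDSMB. Staff who follow the example could miss the board step.

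**Working it through.** The plan states no figure to reproduce. The check is a reading of the rules against two cases, followed by an indication of scale.

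**Case 1: sudden death at home, not suicide, no admission.**

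| SAE item | Met? |
|---|---|
| Breach of trust | No |
| Acute worsening of depressive symptoms | No |
| Hospitalisation | No |
| Self-harm | No |
| Suicide attempt | No |
| Suicide | No |

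The list has 6 items and 1 of them (suicide) is a death. The case matches none. The remaining routes are:

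1. *AE report.* The case fits the AE definition, but the text says who may report and when, not that anyone must. Participants are reminded of this option in the group sessions, which end at week 20. After the post-treatment assessment, the next scheduled one is at six months.
2. *Termination record.* This is compulsory and covers any cause, but it holds only the time point and category. No SAE report or board step is attached.
3. *Investigator access.* The investigator can know of the death, but no stated rule passes it to the IDSMB.

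**Case 2: fall with hospital admission.** Hospitalisation is an SAE item with no condition on relatedness. The SAE entry under Termination criterion then requires IDSMB involvement without exception. The same event is also the example in the health-problems entry, which names only participant and investigator. That entry sends depression and anxiety to another point in the list but makes no such exception for hospitalisation. Both routes apply. The SAE rule can be read as governing, so this is an overlap and not a firm contradiction.

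**Life-threatening events.** They are not named as a category. Most would enter through hospitalisation, self-harm or suicide attempt, so this gap is small.

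**Scale.** Inputs: a 20-week programme (Intervention); follow-up six months after the programme, taken as 26 weeks (Assessment); 250 randomised and 200 planned completers (Power and sample size).

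- Time per participant: 20 + 26 = 46 weeks; 46/52 = 0.885 years.
- Upper person-time, all participants: 250 × 0.885 = 221 person-years.
- Lower person-time, drop-outs counted as contributing none: 200 × 0.885 = 177 person-years.
- Per 1% yearly mortality (assumption): 177 × 0.01 = 1.77 to 221 × 0.01 = 2.21 deaths.

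The document gives neither a mortality rate nor the share of deaths that occur without admission, so no number of missed SAEs can be derived.

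**The case against.** The strongest reply is that no death goes unrecorded. Each one is a compulsory termination category with its time point, the data sit on one central platform, and deaths can be counted by arm. The board's remit is patient safety in general, with SAEs singled out but not exclusive, and nothing withholds termination data from it. The rule linking SAEs to the board concerns whether a participant should continue, which no longer arises after a death, so a separate entry for death is sensible. The AE sentence can be read as describing who has access to the reporting channel and not as making staff reporting optional. The text is a condensed article, and the full protocol may carry the usual seriousness criteria. Terminal illness is an exclusion, which lowers the expected number of deaths. No estimate or test is affected.

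Most of this is true, and it limits the point to classification and escalation. It does not remove it. The article does not leave the SAE definition to another document: it states one, in closed form, and that definition leaves out a foreseeable event. A board that may look at deaths is not the same as a rule that each death must be reported as serious. The objection does settle the weight of the fall example, which is a matter of clarity only. It is also right that the person-years show exposure and not a count of failures.

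**Conclusion.** The concern holds. As written, a non-suicide death without hospital admission is not an SAE, carries no mandatory SAE report to the main site, and has no stated trigger for the IDSMB. The death would still be recorded as a termination, and the board could still learn of it.

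In size, 1 of the 6 listed items is a death, and the exposure is about 177 to 221 person-years. That corresponds to about 1.8 to 2.2 deaths per 1% of assumed yearly mortality, of which only an unknown part would fall in the gap. The conclusion rests on reading the list as exhaustive, as its wording implies, and on the article alone; a wider definition in the full protocol would reduce the problem to a misstatement in the article. The change should be made because the omission concerns safety oversight and is easy to correct. The effect on the efficacy analysis is nil.

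**What to change.** - In Safety considerations, add *death from any cause* and *life-threatening event* to the SAE list.
- In Termination criterion, remove the hospitalised-fall example, or state that any hospitalisation also follows the SAE rule with IDSMB involvement.
- If the full protocol already contains these criteria, bring the article's list into line with it.

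The cost is one phrase in the SAE list, one cross-reference and the matching entry in the case report form. The downside is a few more SAE forms and board consultations. Sample size and analysis do not change.

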### Termination criterion

If a participant withdraws their informed consent during the study, as termination criteria, all data collected up to that point will be removed from the analysis dataset, with the deletion duly documented.In addition, participation in the study may be terminated early under the following circumstances:If a participant does not wish to continue participating or cannot be reached, or fails to attend required study visits (drop-out);If a participant starts an ambulant psychotherapy between the assessment points T0 and T7;If a participant changes their psychoactive medication, continued study participation will be reviewed on a case-by-case basis in consultation with the participant and PI;If health problems arise that are not related to the study content, but may hinder focus-targeted or regular study participation, continued study participation will be reviewed on a case-by-case basis in consultation with the participant and PI. This includes new or worsening physical complaints (e.g. a fall followed by hospitalization), serious events (e.g. the unexpected death of a family member) or psychological complaints (e.g. acute grief – except for depression and anxiety, which are dealt with under point [f]);If any SAE occur, decisions regarding continued participation will always be made by the PI in consultation with the IDSMB, to ensure the participant’s well-being and the appropriateness of their involvement. The jointly made decision will be transparently communicated to the participant;If a participant passes away during the study period;If the PI or study sponsor decides to discontinue participation for specific reasons.

In the event of early termination, the termination criteria are recorded on an individual basis, specifying the corresponding time point and category.

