### Planned statistical analyses

Participants who attend fewer than 75% of sessions (i.e. fewer than 15 group sessions and fewer than three individual sessions) will be excluded from the per-protocol analysis. To prevent an attrition bias, intention-to-treat analyses are used. Missing data will be handled using multiple imputation.

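### Removing every record of a participant who withdraws consent conflicts with the intention-to-treat primary analysis

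*Protocol article*

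**What the plan says.** Two rules on early exit stand together in the section Termination criterion.

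- **Withdrawal of consent.** The rule is mandatory: "all data collected up to that point will be removed from the analysis dataset". The deletion is to be documented.
- **All other grounds.** The rule is permissive: "participation in the study may be terminated early under the following circumstances". The list covers drop-out (unwilling to go on, unreachable, or missing visits), serious adverse events, decisions of the PI or sponsor, and this ground: "If a participant starts an ambulant psychotherapy between the assessment points T0 and T7". Medication changes and unrelated health problems are reviewed case by case. No removal of data is ordered for any of these. The time point and category of each termination are recorded.

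The section Planned statistical analyses gives the purpose of the analysis set: "To prevent an attrition bias, intention-to-treat analyses are used". The section Statistical analysis sub-study 1 makes ITT the primary analysis and multiply imputes missing data in all ITT analyses.

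Three further statements matter. Table 3 places consent and allocation at T0 and measures the PHQ-9 at every point from T1 to T7. The section Intervention says that participants discover their arm in the first group session. The section Primary outcomes defines the outcome as PHQ-9 change both from T1 to T6 and from T1 to T7.

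**The concern.** ITT protects the comparison only if everyone randomised stays in it. The deletion rule takes out people after randomisation on the basis of something that happens after randomisation. Multiple imputation cannot make up for this. It fills gaps in a record from what was observed for that person and others, and here the whole record is gone, baseline included.

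Because the arm is known from session 1, reasons for withdrawing can differ between a psychotherapy programme and a discussion programme run by non-clinical staff. If withdrawal also goes with poorer outcome, the people left in the two arms are no longer comparable. An analysis plan written later cannot restore records that have been deleted.

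A weaker and separate point concerns the other grounds. The article does not say whether ending participation means leaving the programme only or also stopping outcome assessment. If assessment stops, later PHQ-9 values are imputed under an assumption about people who had such an event. This touches the T1 to T7 change most directly. In both programmes "concepts for following supportive treatments are discussed", while starting outpatient psychotherapy before T7 is a ground for ending participation.

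**Working it through.** **1. The plan's own figures.** From Power and sample size: 200 analysable participants, 20% dropout, d = 0.45, alpha 5%, power above 0.80 for the main contrast.

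- N = 200 / (1 − 0.20) = 250. This reproduces.
- Power at 100 per arm, two-sided, with d taken on the SD of change: 0.45 × √(100/2) = 3.18; 3.18 − 1.96 = 1.22; power ≈ 0.89. This agrees with the stated figure. Sidedness and the scale of d are not stated. If d were on the raw SD, power would depend on the pre-post correlation: 0.77 at 0.3, 0.83 at 0.4, 0.89 at 0.5.

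**2. Does deletion threaten power?** Assume that 2%, 5% or 10% of those randomised are deleted and 20% of the rest drop out. Then 250 × (1 − q) × 0.80 leaves 196, 190 or 180 completers, with power of about 0.88, 0.87 or 0.86 on the same scale. The effect is small. The issue is bias.

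**3. Bias in the contrast.** Let q be the share of an arm that is deleted, and g the amount in SD by which deleted participants improve less than those retained. The retained mean then overstates that arm's improvement by q × g. With the same g in both arms:

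shift in contrast (IG minus CG) = g × (q_IG − q_CG)

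The article gives neither q nor g, so all values below are assumptions. Example: 0.8 × (0.05 − 0.15) = −0.080 SD; 0.080 / 0.45 = 18%.

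| Deleted, IG / CG | g = 0.3 | g = 0.5 | g = 0.8 |
|---|---|---|---|
| 5% / 5% | 0 | 0 | 0 |
| 5% / 10% | −0.015 (3%) | −0.025 (6%) | −0.040 (9%) |
| 5% / 15% | −0.030 (7%) | −0.050 (11%) | −0.080 (18%) |

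Percentages are the size of the shift relative to d = 0.45. Exchanging the two arms reverses the sign.

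**4. Type I error.** With 125 × (1 − q) per arm and SE = √(1/n_IG + 1/n_CG), the two-sided error is 5.1% to 6.1% for the 5% / 10% split and 5.6% to 9.2% for the 5% / 15% split. When the CG loses more of its worse participants, the excess rejections favour the CG, not the IG.

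**5. The two exit rules compared.** Consent withdrawal leaves no data at any time point. Drop-out and the other grounds leave all data up to the event, and later values are imputed. Only the first conflicts with ITT as stated. The article names both withdrawing consent and not wishing to continue, but gives no criterion for telling them apart, so one request to stop could lead to either treatment of the data.

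**The case against.** - **The text already separates the two cases.** Someone who merely wishes to stop is a drop-out, with no deletion ordered. This stands. A reader might infer that ending participation after drop-out or a start of psychotherapy also contradicts ITT. The documents do not support that: the wording is permissive, data collected so far remain, and imputing later values is compatible with ITT. What is left is that leaving the programme and ending assessment are not kept apart.
- **Reporting is largely covered.** Deletions and terminations are documented, and CONSORT reporting is promised. This stands, but documenting a deletion does not put the person back into the analysis.
- **The likely direction is conservative.** If dissatisfied or worsening CG members withdraw, deleting them improves the CG mean and shrinks the IG advantage. That is right for this scenario, but the reverse is also possible, and the protocol cannot know which will occur.
- **Data protection may require deletion.** The article cites GDPR compliance, and the consent text is not shown. This stands as a reason to keep deletion for those who ask for it. The article does not give it as the reason for deleting on every withdrawal of consent.
- **Some losses are unavoidable.** People who cannot be reached give no data under any rule. This is true, and it does not bear on data already collected.

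**Conclusion.** The point holds for the deletion rule. As written, removing the full record of anyone who withdraws consent cannot be reconciled with an ITT primary analysis adopted to prevent attrition bias. Under the assumed splits and prognostic differences the contrast shifts by 0.015 to 0.08 SD (3% to 18% of d = 0.45). It shifts by nothing if deletion and prognosis are equal across arms, and its sign is unknown. These sizes rest entirely on assumed rates.

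A reader might take the planned 20% attrition and conclude that the bias could rival the effect itself. It could not on these figures. The 20% is dropout, whose data are kept. Even deleting 20% of one arm and none of the other, at 1.0 SD worse, gives 0.20 × 1.0 = 0.20 SD, or 44% of 0.45.

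The handling of drop-out, psychotherapy start and the other grounds is a point for clarification, not a contradiction. The contrast that the analysis section singles out is pre to post, so psychotherapy begun after T6 leaves it untouched. It does affect the T1 to T7 change, which is also part of the primary outcome.

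**What to change.** Distinguish three events in the protocol and the consent form:

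1. **Stopping the programme.** Keep inviting these participants, and those whose participation would otherwise be ended, to the T6 and T7 outcome assessments if they agree. Record the event and analyse them as randomised.
2. **Stopping further assessments.** Keep all data collected so far in the ITT set and impute later values as planned.
3. **Explicitly requesting deletion.** Delete only in this case. Report the number by arm, and describe the primary analysis set as all randomised participants except these. If data protection requires deletion more widely, say so and describe the set accordingly.

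The cost is a protocol amendment, revised consent wording, and a few extra online assessments on the existing platform. The sample size does not change, and neither does any rule on who continues the programme. The change is best made before any record is deleted.
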